## Abstract

**Introduction:**

Chronic kidney disease (CKD) is increasingly recognised as a growing global public health problem. Early detection and management can significantly reduce the loss of kidney function. The proposed trial aims to evaluate the impact of a community pharmacy-led intervention combining CKD screening and medication review on CKD detection and quality use of medicines (QUM) for patients with CKD. We hypothesise that the proposed intervention will enhance detection of newly diagnosed CKD cases and reduce potentially inappropriate medications use by people at risk of or living with CKD.

**Methods and analysis:**

This study is a multicentre, pragmatic, two-level cluster randomised controlled trial which will be conducted across different regions in Australia. Clusters of community pharmacies from geographical groups of co-located postcodes will be randomised. The project will be conducted in 122 community pharmacies distributed across metropolitan and rural areas. The trial consists of two arms: (1) Control Group: a risk assessment using the QKidney CKD risk assessment tool, and (2) Intervention Group: a risk assessment using the QKidney CKD plus Point-of-Care Testing for kidney function markers (serum creatinine and estimated glomerular filtration rate), followed by a QUM service. The primary outcomes of the study are the proportion of patients newly diagnosed with CKD at the end of the study period (12 months); and rates of changes in the number of medications considered problematic in kidney disease (number of medications prescribed at inappropriate doses based on kidney function and/or number of nephrotoxic medications) over the same period. Secondary outcomes include proportion of people on potentially inappropriate medications, types of recommendations provided by the pharmacist (and acceptance rate by general practitioners), proportion of people who were screened, referred, and took up the referral to visit their general practitioners, and economic and other patient-centred outcomes.

**Ethics and dissemination:**

The trial protocol has been approved by the Human Research Ethics Committee at the University of Sydney (2022/044) and the findings of the study will be presented at scientific conferences and published in peer-reviewed journal(s).

**Trial registration number:**

Australian New Zealand Clinical Trials Registry (ACTRN12622000329763).

Strengths and limitations of this studyThis is the first cluster randomised trial to investigate the effect of pharmacy-led screening of chronic kidney disease (CKD).The sampling strategy used will ensure recruitment of metropolitan, regional and rural pharmacies to provide representative data.Enhanced CKD detection through community pharmacies may also enable earlier commencement of treatment to delay its progression.Pharmacist screening may not necessarily generate the anticipated level of referrals and referral uptakes by general practitioners.The current community pharmacy reform around 60-day dispensing in Australia may impact recruitment of, and participation by, pharmacies.

## Background

Chronic kidney disease (CKD) is a growing public health problem, which affects over 10% of the adult population worldwide.^1^ CKD is defined as sustained kidney damage (presence of proteinuria) and/or reduced kidney function (estimated glomerular filtration rate (eGFR) of <60 mL/min/1.73 m^2^) lasting for at least 3 months.^2^ The global prevalence of CKD is estimated at 9.1%, with high-income countries such as the USA, Canada and Australia the most affected.^1^ There has been a substantial increase in the incidence of people with kidney failure, with people requiring kidney replacement therapies such as dialysis and transplantation increased by 43% over the past 3 decades.^3^ CKD is more prevalent in people with socioeconomic disadvantage, ethnic minorities in the UK and the USA, as well as First Nations peoples in Australia, New Zealand and Canada.^1 2^

Inappropriate use of medications in people with CKD ranges from 24% to 70%.^4–9^ In Australian primary care, approximately 35% of patients are prescribed potentially inappropriate medications based on their kidney function.^10^ As many as 32% of adults with CKD receive inappropriate medications on hospital admission.^11^ The inappropriate use of medications in people with CKD can increase risk of adverse drug events, including hospitalisations and death, and many of these events are potentially preventable by optimising their use.^12^

Inadequate recognition of CKD in primary care is one factor that can contribute to the increased risks of adverse drug events. An Australian study reported that although all patients fulfilled the criteria for a standard CKD definition, only 20% of patients had a documented CKD diagnosis.^11^ Overall, less than a quarter of patients attending general practices with a pathology report consistent with CKD had a term representing kidney disease in their electronic medical records.^13^ Evidence-based guidelines recommend early recognition, referral and management as the most effective approaches to slowing the progression of CKD.^14–17^ If CKD is detected early and managed appropriately, loss of kidney function can be reduced by as much as 50%.^16^

The first Australian Strategic Kidney Disease Action Plan was developed with the aim of preventing and managing CKD through effective use of research, evidence and data.^2^ As part of this plan, collaboration with pharmacists is proposed as a key strategy to improve patient safety.^4^ Community pharmacies represent an underused resource with significant potential to contribute to the early identification and management of individuals at risk of CKD. There are over 5600 community pharmacies spread across metropolitan, regional and remote Australia.^18^ Each person in Australia visits community pharmacies 18 times a year (compared with 6 times for general practitioner (GP) visits),^19 20^ highlighting the opportunity to reach diverse communities, including those in remote regions with limited access to other health services.

Despite mounting evidence to support pharmacists’ involvement in disease screening and medication management,^21 22^ community pharmacists currently have limited role in CKD care. Hence, we propose a novel and yet practical intervention to use the community pharmacy setting to screen for CKD using Point-of-Care Testing (POCT) coupled with a quality use of medicines (QUM) intervention. The use of POCT by pharmacists has been previously evaluated and demonstrated in diabetes and in patients taking warfarin.^23–25^ Small observational studies from the Netherlands, Spain and Canada also explored the effectiveness of using POCT in pharmacies for early detection of CKD and identification of nephrotoxic medication use,^26–28^ while an Australian study evaluated the feasibility of a pharmacist-led CKD screening.^29^

Our pilot work in an Australian context involving 24 community pharmacies and 389 patients found that 52% of screened participants had moderate or high risk of developing CKD, but only 53% of them subsequently had kidney function tests via a pathology provider.^29^ The pilot work highlighted issues such as poor referral uptake by GPs, lack of service remuneration and absence of objective measurements for kidney function.^29 30^ To address these challenges, the proposed trial comprises an improved model of care that involves a more effective collaboration between pharmacists and GPs, including incentives for both, and implementing a POCT for objective measurements of kidney function.

### Trial objectives

The overarching aim is to evaluate the effectiveness of pharmacy-led screening in enhanced detection of previously unknown CKD cases and QUM intervention in optimising medication use for patients with CKD. Specifically, the aim is to:

Determine the effectiveness of a community pharmacy-led screening using POCT on the detection of previously undiagnosed CKD compared to risk assessment alone.Evaluate the impact of community pharmacy-led QUM service informed by POCT in improving the appropriateness of medication use in people with CKD.Investigate the effectiveness of community pharmacy-led CKD screening and QUM service on long-term economic benefits and humanistic outcomes such as health-related quality of life, and consumer well-being and satisfaction.

### Hypotheses

We hypothesise that the use of a POCT with CKD risk assessment (POCT+QKidney Risk Assessment: Intervention Group) in community pharmacies will result in (1) a significantly improved detection of previously unknown CKD cases, and (2) reduced use of potentially inappropriate medications when compared with CKD risk assessment alone (QKidney Risk Assessment: Control Group).

Other hypotheses related to the primary hypothesis are that the Intervention Group will be associated with a statistically significant increase in the proportions of those who are referred to the GP, take up referral with the GP, are newly diagnosed with CKD compared with the Control Group.

Additionally, the incorporation of POCT in conjunction with the QKidney Risk Assessment will lead to enhanced utilisation of kidney beneficial medications (ie, those that slow kidney disease progression), a long-term economic benefit and improved humanistic outcomes.

## Methods

### Study setting and design overview

This study protocol is a multicentre, pragmatic, two-level cluster randomised controlled trial. The reporting of this protocol has been guided by the checklist outlined in the Standard Protocol Items: Recommendations for Interventional Trials (SPIRIT statement, online supplemental appendix 1).^31^

10.1136/bmjopen-2023-079110.supp1Supplementary data

Community pharmacies (clusters) are the unit of randomisation and screening participants are the unit of analysis. The project will be conducted in community pharmacies across three Australian states of New South Wales (NSW), Victoria (VIC), and Queensland (QLD) and later expanded to the Australian Capital Territory.

Community pharmacies will be selected from geographical groups of co-located postcodes to form clusters within the top 50 kidney disease hotspot areas identified by Kidney Health Australia.^14^ Co-located pharmacies within a cluster represent a local community that will all receive the same service model to reduce contamination bias. Pairs of clusters matched by characteristics such as location and socioeconomic status^32^ will be randomly allocated to the intervention or control groups. Objective geographical access is described using the Modified Monash Model (MMM). Consistent with the Australian Government Department of Health and Aged Care’s definition used in the Rural Health Multidisciplinary Training Program,^33 34^ the MMM for this study was broadly stratified into Metropolitan (MM1) and Rural (MM2–7) categories. Given there were no postcodes classified as ‘MM6 – Remote Communities’ or ‘MM7 – Very Remote Communities’ identified within the top 50 kidney disease hotspots, the Rural categorisation was constrained to MM2–5. The number of community pharmacies to be targeted is determined based on the respective population sizes of the states, with proportional pharmacy distributions across Metropolitan and Rural settings. Therefore, based on the population of the states and the percentage contribution of each state, a total of 122 community pharmacies will be recruited from the three states with 1:1 control:intervention allocation, representing 50 pharmacies from NSW (38 Metropolitan vs 12 Rural), 40 from VIC (30 vs 10) and 32 from QLD (20 vs 12). Given the proximity of some of the NSW pharmacies, we have expanded our recruitment to include pharmacies in the Australian Capital Territory.

After the identification of the initial round of postcodes, these were stratified, and colour coded by the geospatial expert (VV) based on socioeconomic status and remoteness to ensure a balanced representation. The allocation into the intervention and control arms was randomised centrally at the University of Sydney by the project manager.

#### Selection of community pharmacies

Community pharmacies within identified postcodes will be identified by triangulating sources such as ‘Yellow Pages’, ‘Google’ and the pharmacy finder in the Pharmacy Guild’s website. All identified pharmacies that are approved to dispense Pharmaceutical Benefits Scheme (PBS) medicines (Australia’s universal medicine subsidy programme); have a separate or private counselling area; accredited by an approved pharmacy accreditation programme; have FRED/Z dispensing software will be eligible to participate in the study. Of note, pharmacies without FRED/Z systems but have capacity for manual data entry may be considered for inclusion. Prior to participating in the trial, eligible pharmacies will be required to complete an online training and a baseline survey on existing practices on any screening and QUM services in different chronic diseases including CKD. All identified pharmacies will be contacted by the research team to participate in the study and, if consented to participate, provided with relevant training and onboarding information.

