### Baseline evaluation

At the beginning of the study, participating pharmacies will be required to complete a baseline survey that includes questions on pharmacy characteristics, existing professional services (remunerated and non-remunerated) and strategies and capacity for implementing these services. The information collected will be used to inform the comparability of the two arms in the trial and health economic analysis. All data entered by participant pharmacists into the study software will be extracted to generate quantitative data to enable the trial process evaluation.

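### On the most natural reading, postcode groups were allocated before their pharmacies were recruited, with no concealment step described, so which pharmacies enter can depend on the arm

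*Protocol article*

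**What the plan says.** **Allocation.** Study setting and design overview says: "After the identification of the initial round of postcodes, these were stratified, and colour coded by the geospatial expert". It continues: "The allocation into the intervention and control arms was randomised centrally at the University of Sydney by the project manager". Both statements are in the past tense, and the thing stratified is a set of postcodes. The same section says that co-located pharmacies in a cluster will all receive one service model.

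**Recruitment.** Selection of community pharmacies is in the future tense: "Community pharmacies within identified postcodes will be identified by triangulating sources such as" public directories. Pharmacies that meet the other criteria and "have FRED/Z dispensing software will be eligible to participate in the study". An exception follows: "pharmacies without FRED/Z systems but have capacity for manual data entry may be considered for inclusion". Then: "All identified pharmacies will be contacted by the research team to participate in the study and, if consented to participate, provided with relevant training".

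**A competing description.** Earlier in Study setting and design overview, community pharmacies are called the unit of randomisation, and matched pairs of clusters are still to be allocated (future tense).

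**Baseline survey.** Of the survey completed by participating pharmacies, Baseline evaluation says: "The information collected will be used to inform the comparability of the two arms in the trial".

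**The concern.** In a cluster trial, randomisation protects the comparison only if the units that enter are fixed before the arm is known, or are chosen without regard to it. If a postcode group already has an arm when its pharmacies are approached, three later decisions are open to knowledge of that arm: whether a pharmacy accepts, whether its pharmacists complete the arm's entry requirements, and whether a pharmacy without the named software is let in.

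The arms ask for different work. Intervention pharmacies take on point-of-care testing, a medication review service and sessions of 20 to 45 minutes. Control pharmacies give a risk assessment with advice and fact sheets in 20 to 30 minutes. Intervention pharmacists complete four training modules against three for control, and device competency is an entry condition in the intervention arm only (Selection of pharmacists).

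Pharmacies that accept the heavier arm may be more service-oriented or better connected to local GPs. The Background reports poor GP referral uptake in the pilot, so GP links could plausibly affect both new diagnoses and medication changes. A difference between arms in the kind of pharmacy enrolled would then be mixed with the intervention effect on both primary outcomes.

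**Working it through.** The claim concerns the order of steps and rests on no figure in the plan. The texts are set side by side first. The plan's figures then show what can and cannot be said about size.

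**1. Order of steps**

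| Step | Place in the protocol article | How it is written |
|---|---|---|
| Postcodes identified and stratified | Study setting and design overview | past tense |
| Arms randomised by the project manager | same | past tense |
| Pairs of clusters allocated | same, earlier paragraph | future tense |
| Pharmacies in those postcodes identified | Selection of community pharmacies | future tense |
| Eligibility, software exception, contact, consent | same | future or conditional |
| Site randomisation, then consent | Table 1 | in that row order, both under Baseline |

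The completed randomisation follows directly on postcode stratification, and the search for pharmacies takes place inside postcodes already chosen. With one service model per postcode group, location determines the arm. Allocation first is therefore the most natural reading. The future-tense allocation and the pharmacy as randomised unit do not fit it. Table 1 agrees with it but proves little, because its rows share one column and are not strictly in time order.

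**2. What limits selection by arm, and what does not**

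- All identified pharmacies are to be contacted. This governs who is invited, not who accepts or is admitted by exception.
- Pairs are matched on characteristics such as location and socioeconomic status. This balances areas, not the pharmacies that agree within them.
- The adjusted model (Data analysis plan) uses age, gender, blood pressure, BMI, socioeconomic status and pharmacy location. None measures pharmacy motivation, GP links or software.
- The baseline survey covers pharmacies that have already come in. It can describe an imbalance but cannot prevent one.
- The software exception has one stated condition, capacity for manual entry. The article gives no rule beyond that, no decision-maker and no statement that the decision is made without knowledge of allocation.

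**3. Scale**

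Inputs from Sample size: 10% against 15%, 80% power, ICC 0.05, 30 participants per cluster. Two-sided alpha of 0.05 is from Data analysis plan.

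- Individually randomised size: 686 per arm.
- Design effect: 1 + (30 − 1) × 0.05 = 2.45.
- Clusters per arm: 686 × 2.45 / 30 = 56.02, rounded up to 57. The plan's figure reproduces.
- With 61 per arm, the total is 61 × 2 × 30 = 3660, and power is about 83%.

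More clusters reduce random error and leave selection bias as it is.

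The same inputs imply a between-pharmacy standard deviation in the diagnosis rate of sqrt(0.05 × 0.10 × 0.90) = 0.067, or 6.7 percentage points. If selection moved the intervention pharmacies by d standard deviations, the bias would be d × 6.7 points, against a target difference of 5 points. The documents give nothing from which d could be estimated.

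**The case against.** The strongest reply is that the order is inferred. No sentence states that allocation came before pharmacy recruitment, tense is used loosely (the same allocation is both future and past), and one paragraph names the pharmacy as the unit of randomisation. This stands in part. It makes the point one to reconcile and lowers confidence, but it does not give an equally natural alternative reading. If pharmacies were in fact consented first, one sentence saying so settles this part.

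A second reply is that invitation wording and the timing of disclosure belong in the full protocol, and that knowledge of the allocation is documented only for the project manager. On its own, the missing rule for the software exception would indeed be mere detail. It matters here because it sits after an allocation that appears to be complete.

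Four stronger readings are tempting and are not supported:

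- *That entry did depend on the arm.* The article shows only that it could.
- *That unequal use of the exception would leave the primary medication outcome less complete in one arm.* The outcomes section says primary outcomes are determined from data collected from GPs, so this is not shown.
- *That control pharmacies do no more than compute a risk score.* They also give lifestyle advice, fact sheets and, for known CKD, counselling on medications to avoid. The contrast in workload is real but smaller than that.
- *That the bias can be put at a figure.* For example, 0.25 to 0.5 standard deviations would give 1.7 to 3.4 points. The shift has no source, so the result only restates the assumption.

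**Conclusion.** The concern holds as a weakness in the design as described, with medium confidence. On the most natural reading, a pharmacy's arm is settled before it is found, assessed and consented, and nothing described keeps that arm from recruiters or pharmacies. Acceptance and admission under the exception can therefore differ by arm, and neither the matching nor the planned adjustment addresses the pharmacy traits most likely to matter.

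The size of any bias cannot be computed. The 6.7-point between-pharmacy standard deviation shows only that pharmacies are expected to vary by more than the 5-point target, so that arm-related selection would not be negligible by construction. The conclusion rests on two assumptions: that the past-tense account of allocation is accurate, and that no concealment step exists in material not shown. It should be changed where recruitment is still open, and the conflicting statements on unit and timing should be reconciled in any case.

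**What to change.** 1. State the order of postcode selection, allocation, pharmacy identification, eligibility and consent, and reconcile the unit of randomisation with it.
2. For every pharmacy still to be recruited (later postcodes, replacements, the Australian Capital Territory), use one arm-neutral invitation. Settle eligibility, consent and the baseline survey first. Only then disclose the arm and assign arm-specific training.
3. Replace the open-ended software exception with a fixed rule, applied by someone without knowledge of the allocation.
4. For all pharmacies, including those already enrolled, report by arm the numbers invited, refused, admitted by exception, enrolled and withdrawn after disclosure.

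**Cost.** This reorders existing steps, changes the invitation text and adds a tally. Some pharmacies may withdraw once they learn their arm. That moves arm-related refusal to a point where it can be seen and counted but does not abolish it, and the allowance is only four clusters per arm (57 to 61). Concealment may also be imperfect once one pharmacy in a postcode group knows its arm, because its neighbours share it. For pharmacies already recruited, reporting is all that remains.

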#### Sample size

Sample size selection and estimation was performed based on the CKD diagnosis. Using the GRT sample size calculator,^35^ it is estimated that the intervention will increase diagnosis from the current CKD prevalence of 10% to between 15% and 20%, an increase of 5%–10%. Sample size is estimated based on a 5% increase in diagnosis of CKD. With 80% power, alpha of 0.05 and intraclass correlation coefficient (ICC)=0.05, at least 57 clusters are required per arm. Based on our sampling model, cluster size has been increased to 61 per arm to account for attrition. With an average number of 30 participants per cluster, the total sample size to be targeted is 3660. Based on previous study^11^ that showed a reduction of inappropriate medications in CKD from 32.3% to 17.5% (an approximate reduction of 15%), with 90% power, alpha=0.05 and ICC of 0.05 and a cluster size of 30 per cluster, 19 clusters in each arm are required (38 clusters in all) with a sample size of 1140 for the other primary outcome, that is, change in inappropriate medication use. The sample size required for the diagnosis outcome is, therefore, sufficient to cover the sample size required for the medication changes outcome.

